**Fig. 2 Fig2:**
[figure not shown]
Map of study clusters showing randomly allocated clusters

#### Individual participant eligibility

Inclusion criteria to be enrolled into menstrual monitoring (to detect pregnancy) are being a married woman between the ages of 13 and 49 years: being resident in the study cluster (whether at her husband’s or parental home); could become pregnant (i.e. she and her husband have not had permanent sterilization such as tubal ligation or vasectomy, has not attained menopause nor had a hysterectomy); and consents to being asked about their menstrual status once every 4 weeks.

Inclusion criteria for a woman to be enrolled into trial follow-up include the following: a married female aged 13 to 49 years with a positive pregnancy test, at less than 20 weeks’ gestation, who is able to provide informed consent/assent and respond to survey questions. The gestational age is estimated from the date of the last menstrual period (LMP) as recalled by the PW, which is cross-checked against LMP dates recorded in the menstrual monitoring register during menstrual monitoring. If a PW has already visited a health facility for an ultrasound test, this report is also checked before enrolling the woman.

Exclusion criteria include non-consent and/or unable to respond to questions, ≥ 20 weeks’ gestation from LMP (or uterus clearly visible above the level of the umbilicus if LMP is not recalled/not available) and not planning to reside in the study cluster for most of her pregnancy.

Although the study participants give consent, their family members are also encouraged to participate in home visits and women’s groups. We will also ask for consent from husbands or adult male household members (or mother-in-law if no adult male), to measure their diets in addition to the PW.

### Who will take informed consent? {26a}

Letters of approval to work in selected clusters were received from municipality officials by field managers employed by HERD International before undertaking the census. Household heads provided written/thumbprint consent to collect census data.

All consent for individual participation (using signature or thumbprint) is taken by interviewers at the beginning of menstrual monitoring and again at enrolment into follow-up when pregnancy is detected. After obtaining written consent, interviewers take oral consent at subsequent menstrual monitoring and trial follow-up visits. A participant is free to withdraw consent or refuse data collection on any of these occasions. Interviewers will take written consent from the married woman herself where she is 18 years or above. For adolescents 13 to 17 years, interviewers will take written consent from guardians and written assent from the adolescent, and both shall be required for the girl to participate. Supplementary annexes 3, 4, 5 and 6 provide the trial participation information sheets and consent forms in English (copies in Nepali and Awadhi available on request).

### Additional consent provisions for collection and use of participant data and biological specimens {26b}

This trial does not involve collecting biological specimens for storage. Every consent form has a clause asking permission to share the anonymised data collected in this study with other researchers to conduct secondary analyses and to revisit the participant for future follow-up studies, should the need arise.

## Interventions

### Explanation for the choice of comparators {6b}

We compare intervention with control clusters, where women do not receive the interventions but have access to routine antenatal care services within the government health system. Menstrual monitoring in both intervention and control clusters may mean pregnancies are detected earlier, and women may receive ANC and/or IFA earlier, than outside the study area.

### Intervention description {11a}

#### Intervention staff recruitment and training

Six certified auxiliary nurse midwives are employed by HERD as nutrition assistants (NAs) to deliver tailored home visits to PW and facilitate PLA women’s groups in 4–5 intervention clusters each. Training of NAs will involve role-play practice sessions and field testing of intervention activities. Topics include (i) health consequences of anaemia in pregnancy and anaemia prevention/treatment; (ii) diet in pregnancy and how to increase iron intake and bioavailability; (iii) communication skills; (iv) how to engage families in dialogue and problem solving; (iv) use of Hemocue to measure Hb levels; (v) use of mobile phones/tablets and CommCare for recording and reporting of intervention activities; (vi) how to run women’s groups following a PLA intervention manual.

A diagram summarising the home visiting and PLA interventions is shown in Fig. 3.

**Fig. 3 Fig3:**
[figure not shown]
Components of the combined home visiting and Participatory Learning and Action (PLA) interventions

#### Home visiting intervention

Home visits are designed to work synergistically to encourage PLA group attendance, to reach women who cannot / do not leave their homes and to engage family members. Each home visit will comprise dialogical counselling, home-based anaemia screening and tailored provision of IFA. The NA will visit each PW twice at home, first at 12 to 21 weeks and second at 22 to 26 weeks. Ideally the gap between visits will be 4 to 6 weeks, unless logistical constraints imposed by the COVID-19 pandemic disrupt activities.

##### Home-based tailored dialogical counselling

We will take a *dialogical* approach to engage pregnant women and their families to think critically about the causes of anaemia in pregnancy in their household and community. The NA will engage pregnant women and their families in a cycle of action and reflection: (1) listening for the key issues and emotional concerns of the household; (2) promoting participatory dialogue about these concerns and (3) planning and taking action about the concerns that are discussed. At the first and second home visits, the NA will use stories and inductive questioning to trigger dialogue and reflection [66]. Stories will directly address issues from our formative research. We will train the NA about common issues that may arise and provide a discussion and reference manual with examples of actions that pregnant women and their families could take. Families will make specific action plans to address the issues that are relevant for their family and in the second visit these will be reviewed, and a different story used to trigger discussion and reflection. The tailored counselling aims to support women and their families to take actions to change dietary practices, take IFA and deworming tablets, attend PLA groups and access antenatal care. If the NA observes any pregnancy danger signs, as per the government’s standard treatment protocol [45], she will advise the woman to seek care straight away from the nearest appropriate health facility.

##### Anaemia screening and tailored iron-folic acid therapy

At each home visit, following the nutrition counselling, the NA will measure the PW’s haemoglobin concentration using a hand-held Hemocue Hb 301+ analyser, measure her mid-upper arm circumference (MUAC) with a SECA tape (93/42/EEC) to assess thinness, and explain the results. Following GoN guidelines, the NA will advise the PW to take IFA as follows:
Not anaemic (Hb ≥ =11 g/dL), one IFA tablet (60 mg elemental iron and 400 μg folic acid) per day.Mildly or moderately anaemic (Hb 7–10.9 g/dL), two IFA tablets (120 mg elemental iron and 800 μg folic acid) per day.Severely anaemic (Hb < 7 g/dL), the NA will immediately refer the PW for a blood transfusion at a higher health facility.

At visit 1 (at 12 to 21 weeks’ gestation), the NA will provide sufficient IFA tablets for a period of 4–10 weeks until her second visit, at 22 to 26 weeks’ gestation. For all women, NAs will emphasise the importance of increasing dietary diversity and consuming micronutrient-rich food. For women with low (< 230 mm) or very low (< 210 mm) MUAC, the NA will also emphasise the importance of consuming additional calories through more frequent and/or larger meals and taking adequate rest. For women with MUAC ≥ 300 mm, the NA will stress the importance of keeping active during pregnancy and avoiding sugary or fatty foods and large portions of rice.

After repeating the haemoglobin and MUAC measurements at the second visit, the NA will explain to the woman how her anaemia and thinness status have changed and provide the appropriate IFA dose. She will also assess compliance to IFA by asking the PW about their tablet consumption and checking used blister packs. At visit 2, the NA will provide a single (400 mg) albendazole tablet if the PW has not already received it as per Nepal’s national protocol for women in their second trimester.

The NA will record details of haemoglobin and MUAC readings, IFA and albendazole tablets provided on the Trial Participation Card (TPC) at each visit to enable participants to show health workers what treatment they have been receiving. The NAs will make two copies of discussion action sheets to record actions agreed to reduce anaemia based on the issues identified. One copy will be given to the PW’s family, and the other copy will be kept by the NA for reference. The NA will also record Hb, MUAC, IFA and albendazole given, and the actions agreed upon with the PW’s family on an electronic data collection form just after the visit is concluded. The NA will not enter data on the tablet or phone during the visit to allow fluid interpersonal interaction but will take a photograph of the TPC and the discussion action sheet before leaving the home.

The modality of the home visiting intervention is shown in Fig. 4.

**Fig. 4 Fig4:**
[figure not shown]
Modality of the home visiting intervention

#### Participatory Learning and Action women’s group (PLA) intervention

In the intervention arm, the NA, together with the local FCHV for that cluster, will facilitate monthly groups at a convenient place and time for community members. As FCHVs are mandated by the health system to hold monthly mothers’ groups, we will work through these groups where they already exist and revitalise them where they are inactive.

The groups will run for a 15-month period, from the last month of menstrual monitoring consent to (about 1 month before the first enrolment) until after the last enrolled woman has completed 30 ± 2 weeks gestation. NAs, who are locally recruited and trained, will train the FCHVs on the PLA meeting manual each month and the FCHVs will assist the NAs in group facilitation. Groups are open to anyone who is interested, and participation is voluntary. As restrictive gender norms can prevent women’s participation in mixed groups, the first 10 meetings will be exclusive to women. Men will be invited to a large community planning meeting and groups will discuss how they would like to engage with men thereafter.

The PLA cycle will consist of four phases (1) problem identification, (2) planning together, (3) strategy implementation and (4) strategy evaluation. During the ‘problem identification’ phase, over 6 monthly meetings, groups are introduced to the PLA method and discuss local definitions and beliefs about the causes and symptoms of anaemia, and local beliefs around taking IFA supplements. They will then discuss barriers to good nutrition to improve anaemia, and barriers to uptake of IFA supplementation during pregnancy. During the ‘planning together’ phase, over 3 monthly meeting groups prioritise problems that they would like to address and plan and implement a community meeting to engage the wider community. Groups will then lead on the implementation of these strategies in Phase 3 and will continue discussing new topics related to anaemia in pregnancy. They will evaluate the effect of their actions in Phase 4 by reflecting on the original problems and progress in solving them. Then they may reformulate strategies to begin another phase of implementation.

During the PLA cycle, facilitators use a pictorial meeting manual which contains varied triggers for discussion—such as a story, a quiz or game—which are often used with picture cards. These focus on iron- rich foods and how to increase bioavailability, improve IFA compliance, reduce side effects and manage nausea and minor pregnancy ailments, and when to seek care for more serious problems.

### Criteria for discontinuing or modifying allocated interventions {11b}

We do not expect that the tailored counselling or PLA women’s groups to have any negative effects upon trial participants, but some women may experience side effects from consuming IFA or from deworming. Side effects commonly experienced from IFA include constipation and indigestion [1, 89], but these tend not to be serious. Recent studies have also indicated that iron supplementation may increase susceptibility to infections but that this is more common in children than adults [90]. Interviewers will collect data on side effects of IFA and on morbidity of women during the 30 ± 2-week interviews and NAs will ask women about side effects and advise how to mitigate them during counselling sessions and at women’s groups. In exceptional cases, if the higher IFA dose is not being tolerated, the NA may advise the woman to reduce intake from two to one tablet per day. All women who are feeling unwell at the time of interaction with the NA or data collector are advised to seek care at their nearby health facility or at a higher care centre where needed.

### Strategies to improve adherence to interventions {11c}

Nepal’s national protocol is to provide PW with IFA from 20 weeks’ gestation onwards till 45 days post-partum from all health facilities, outreach clinics and FCHVs. Doubling the dose for anaemic women is in the GoN protocol but usually not practised. We will orient all health workers at the health facilities in/near intervention areas, and the district and regional hospitals, about the intervention and the distribution of IFA and albendazole tablets by the NA during home visits and encourage them to practice administration of double dose for women who have been identified as anaemic in line with NA prescription. NAs will ask women to show their home visit TPC records of Hb, MUAC, IFA and albendazole tablets to health workers at the beginning of each ANC consultation to ensure women are not prescribed double doses of IFA or albendazole. The NAs will visit health facilities every month and provide a list of the enrolled participants and the number of tablets provided to them to avoid duplication. For more distant health facilities, or where visiting health facilities is restricted by COVID-19, information is sent by email or SMS and NAs phone health workers to ensure the information has been received.

NAs attend monthly meetings with intervention coordinators to reflect on the previous PLA meeting and plan for the next. Through discussion and role-play, facilitators develop common methods of holding meetings. Whilst the trial surveillance system is getting established, a 1-month ‘run-in’ of women’s groups allows time for groups to get established before the first ‘full-trial’ PW enrols. The picture cards and women’s group manual can be modified as needed to ensure that content is realistic, understandable, culturally appropriate, visually appealing, and motivating, but any changes will be applied across all intervention clusters.

### Relevant concomitant care permitted or prohibited during the trial {11d}

Women who receive home visits and tailored doses of IFA and deworming are strongly discouraged from taking additional doses of micronutrients or additional deworming. NAs and interviewers encourage PW to seek concomitant care for any illnesses they may be experiencing which are reported during interactions. If the interviewer or NA detects severe anaemia, they give the PW a referral slip, and advise her to go immediately to the district hospital or other referral centre where transfusions are available.

### Provisions for post-trial care {30}

We do not envisage complications that would require compensation but have necessary insurance arrangements in place.

### Outcomes {12}

All outcomes are measured during 30 ± 2-week interviews and are listed in Table 1 below.

**Table 1 Tab1:** Trial outcomes and indicators on the impact pathway

CAPPT trial outcomes	Effect measure to compare arms/summary statistic
**Primary outcome** at 30 ± 2 weeks	
Haemoglobin concentration ascertained from a Hemocue 301+ analyser reading (Hb g/dL)	Difference/mean
**Secondary outcomes** at 30 ± 2 weeks	
Prevalence of anaemia (% Hb< 11.0 g/dL)	Odds ratio/proportion
Mid-upper arm circumference (cm)	Difference/mean
Mean probability of adequacy (MPA) of 11 micronutrients including vitamin A, riboflavin (B_2_ ), niacin (B_3_ ), pyridoxine (B_6_ ), cobalamin (B_12_ ), thiamine (B_1_ ), folate (B_9_ ), vitamin C, iron, zinc and calcium;	Difference/mean
Total number of ANC visits a health facility	Ratio/mean
**Indicators on the pathway to impact to be compared between arms** at 30 ± 2 weeks	
IFA tablets consumed by time of measurement at 30 ± 2 weeks	Ratio/mean
Usual energy intake (kcal/day)	Difference/mean
Usual dietary iron intake (excluding supplements) (mg/day)	Difference/mean
Uptake of methods used to improve bioavailability	Ratio/mean
Nutrition knowledge score	Ratio/count

The primary outcome of the trial is mean haemoglobin concentration in g/dL ascertained from a Hemocue 301+ analyser reading. Secondary outcomes are prevalence of anaemia (% Hb< 11.0 g/dL), mid-upper arm circumference (cm) and mean probability of micronutrient adequacy of 11 micronutrients including vitamin A, riboflavin (B_2_), niacin (B_3_), pyridoxine (B_6_), cobalamin (B_12_), thiamine (B_1_), folate (B_9_), vitamin C, iron, zinc and calcium.

Indicators to compare between arms to assess pathways to impact include the following: count of ANC visits at a health facility, number of IFA tablets consumed during pregnancy, intakes of energy (kcal/day) and dietary iron excluding supplements (mg/day), a score of bioavailability-enhancing behaviours (comprised of avoiding tea and coffee at or near mealtimes, use of vitamin C-rich foods with food and IFA tablets, use of sprouted pulses or grains and spreading of haem-iron foods over 2 eating occasions), recall of nutrition knowledge indicators pertaining to iron-rich foods, importance of IFA and ways to improve bioavailability of iron.

To describe intervention implementation and potential mechanisms by which the intervention and its components may have an effect, we also collect process outcomes given in Table 2. Exposure to PLA groups, number of home visits and side effects will be reported in the main trial paper, together with factors which emerge as key indicators of intervention fidelity. Other process indicators may be reported in one or more separate publications. Process indicators include weight gain in pregnancy, gestational age at first ANC, amounts of promoted foods consumed, health literacy, social networks and social norms. For assessment of the effect of the intervention upon intra-household food allocation, we measure ratios of MPA, energy adequacy and iron intake between the PW and her husband (or senior household member).

**Table 2 Tab2:** Process indicators

**Intervention exposure and activities**	
Number of home visits received (0, 1 or 2)^1^	
Family actions agreed upon in the home visit	
Which family members took part in the home visit interaction	
Doses of IFA prescribed	
Exposure to PLA community strategies^1^	
Whether any family members attended PLA groups	
Which family members attended	
**Social and behaviour change processes**	
Health literacy	
Social norms	
**IFA and ANC processes**	
Numbers of IFA tablets consumed in relation to those prescribed	
Uptake of any antenatal care	
Quality of antenatal care	
Gestational age at first ANC visit	

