#### Outcome measurement in the third trimester of pregnancy

As listed in Table 1, all primary, secondary and process outcomes are measured at 30 ± 2 weeks. Although ideally during the 28-to-32-week window, due to potential disruption that the ongoing COVID-19 pandemic may cause, an outcome may be collected any time up to delivery as gestational age at measurement will be adjusted for in all analyses.

Dietary interviewers use an adapted quantitative 24-h dietary recall tool [98] to measure dietary intakes of PW and their husbands or another ‘senior’ male (or a female household head if there are no men). Recalls are taken twice on non-consecutive days after between 28 and 32 weeks, including typical and atypical (celebratory and fasting) days. Daily nutritional intakes are calculated using (i) a list of locally available foods; (ii) quantified intakes of each food, estimated using a combination of weighed methods (using food models) and a photographic atlas of graduated portion sizes [99] and (iii) a Food Composition Table that integrates nutritional composition data from Nepal [100–102], India [103], Bangladesh [104], USA [105], UK [106, 107] and published back-of-pack information from local foods [102].

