Analysis of secondary and impact pathway outcomes (Table 1) and of process indicators (reported in 1 or more separate publications (Table 2)) will follow a similar methodology. We will use linear regression for continuous outcomes, logistic regression for binary outcomes, ordinal logistic regression for ordinal outcomes and negative binomial regression for ‘count’ outcomes such as number of IFA consumed. For continuous and count outcomes, before analysis of intervention effectiveness, the distribution will be examined and in the event of skewed or heaped data transformations such as log will be considered, or methods will be adapted such as for zero-inflation. For energy, iron and other micronutrients, which are (almost) ubiquitously consumed, we will use our duplicate measure to account for the wide intra-individual variability with a nonlinear random effects model and person-specific random effects (the National Cancer Institute method). For intakes of recommended foods that are only episodically consumed but also have wide within-person variance, we use a two-part model where the probability of consumption is estimated using a multilevel logistic regression, the amount consumed on consumption days is estimated by fitting a multilevel nonlinear regression model and the error terms of the two parts are correlated [108].

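### Gestational age at first ANC visit, analysed by the general linear-regression rule, compares attenders only and is biased against an intervention that aims to raise attendance

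*Protocol article*

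**What the plan says.** Table 2 of the protocol article, under IFA and ANC processes, lists "Gestational age at first ANC visit". The Outcomes {12} section repeats it: "Process indicators include weight gain in pregnancy, gestational age at first ANC, amounts of promoted foods consumed".

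On timing, the section on outcome measurement in the third trimester says that "all primary, secondary and process outcomes are measured at 30 ± 2 weeks". It allows for pandemic disruption: "an outcome may be collected any time up to delivery as gestational age at measurement will be adjusted for in all analyses".

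On analysis, the section Statistical methods for primary and secondary outcomes {20a} says, in the paragraph after Table 4, that the analysis "of process indicators (reported in 1 or more separate publications (Table 2)) will follow a similar methodology". It then gives the model by outcome type: "We will use linear regression for continuous outcomes, logistic regression for binary outcomes, ordinal logistic regression for ordinal outcomes", followed by negative binomial regression for counts. It allows for skewness, heaping and zero-inflation. It names no method for a value that does not yet exist at the interview.

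On the aim of the intervention, the home-based counselling section says that women and families are supported to "take IFA and deworming tablets, attend PLA groups and access antenatal care".

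**The concern.** A woman who has not attended by her interview has no gestational age at first visit. Her time to first visit is right-censored at the interview. A linear model on weeks leaves her out.

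Being left out is not independent of arm. Home visits at 12–21 and 22–26 weeks are meant, among other things, to bring women into antenatal care. A woman brought in after a home visit enters the intervention mean, often with a late value, while her counterpart in a control cluster contributes nothing. The arms are then compared within subsets formed after randomisation by a behaviour under test. Baseline covariates do not repair this. Nor does the planned adjustment for gestational age at measurement, because the women without a visit are still excluded.

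At stake is the reading of one pathway step. The background section on IFA supplementation and antenatal care argues that care must start earlier for women to take more IFA, and this indicator measures that start directly. An estimate biased towards no benefit, or towards delay, could misdirect the process evaluation.

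**Working it through.** The protocol gives no figure for this indicator, so there is none to reproduce. It also gives no rate of women without a visit by 30 weeks. All sizes below rest on stated assumptions.

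**Step 1: two women per arm, no distribution needed.** In control, one woman first attends at 14 weeks and one has not attended by interview. The attenders' mean is 14. In the intervention arm, the matching women attend at 14 and at 23 weeks. The mean is (14 + 23)/2 = 18.5. The difference is +4.5 weeks, although no woman attended later and one attended earlier.

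**Step 2: formula.** Let attendance by interview be pC in control and pI in intervention, the mean among existing attenders m, and the mean start of the added attenders g. With nobody else changed:

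attenders-only difference = ((pI − pC)/pI) × (g − m)

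- 80% to 90%, m = 18, g = 28: (0.10/0.90) × 10 = +1.1 weeks.
- 90% to 95%, m = 20, g = 24: (0.05/0.95) × 4 = +0.2 weeks.
- If g is close to m, the difference is about 0, although attendance has risen.

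The sign therefore turns on whether new attenders start later than existing ones.

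**Step 3: simulation (1,000,000 women per arm).** Assumptions:

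- First-visit gestation among potential attenders is normal with SD 6 weeks.
- 42% of them start after 4 months. The 42% is the protocol's figure for rural women in 2016; applying it to attenders is an assumption. With 4 months = 17.4 weeks, the mean is 17.4 − 6 × 0.202 = 16.2 weeks.
- A further 5–25% of women have no visit.
- The intervention brings in 50–67% of these.
- Interviews are uniform over 28–32 weeks.

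Attenders-only difference in weeks, intervention minus control:

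| Control women without a visit | New starts at 18–28 wk, others unchanged | New starts at 13–20 wk, others unchanged | New starts at 18–28 wk, others 1 wk earlier | New starts at 13–20 wk, others 1 wk earlier |
|---|---|---|---|---|
| 5% | +0.2 | 0.0 | −0.7 to −0.6 | −0.9 |
| 10% | +0.4 to +0.5 | 0.0 | −0.5 to −0.4 | −0.8 |
| 15% | +0.6 to +0.7 | +0.1 | −0.3 to −0.1 | −0.8 |
| 25% | +1.0 to +1.3 | +0.1 | +0.2 to +0.5 | −0.7 |

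For comparison, the all-women difference in mean time without a visit, restricted to 28 weeks, runs over the same rows:

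- −0.1 to −0.8 (18–28 wk, others unchanged)
- −0.3 to −1.9 (13–20 wk, others unchanged)
- −1.0 to −1.6 (18–28 wk, others 1 wk earlier)
- −1.2 to −2.6 (13–20 wk, others 1 wk earlier)

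In every scenario the attenders-only figure understates the benefit. Apparent delay of any size needs late new starts. A true 1-week gain among other women changes sign only at 25% non-attendance with late starts.

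**Step 4: uniform shift.** In a second model (latent mean 21, SD 8 weeks), every woman starts 2 weeks earlier. The attenders-only difference is −1.4 weeks: the right sign, but diluted.

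**The case against.** The strongest reply is that the protocol never assigns a model to this indicator. It maps models to outcome types, calls the approach to process indicators similar rather than identical, and leaves analysis detail and missing data to a statistical analysis plan that is not shown. A categorised version would fall under ordinal logistic regression. All of this is true, and a reader should not infer that the protocol names linear regression for this variable or says that non-attenders are dropped. What remains is that gestational age in weeks is continuous, the stated rule for continuous outcomes is linear regression, and none of the listed adaptations covers a value that does not yet exist. Following the rule as published gives the attenders-only comparison.

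A reader might also infer that the trial will report a delay. The working does not support that. The first home visit is at 12–21 weeks, so attendance it prompts may be early, and then the spurious difference is about 0 to +0.1 weeks. The protocol also notes that menstrual monitoring in both arms may bring care forward, which favours the low end of the non-attendance range. Dilution is the general result; reversal is conditional.

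Finally, a reader might infer that the trial's conclusions on antenatal care are unsafe. They are not. The number of ANC visits in Table 1 is a count in which a woman with none scores zero. Table 2 also lists uptake of any ANC separately, which would show a rise in attendance beside any shift in timing. It would not correct the timing estimate itself. This indicator is not flagged for the main trial paper and is not among the mediators named in the process evaluation section.

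**Conclusion.** The point holds as a minor one. Under the protocol's general rule, gestational age at first ANC visit is compared among women who attended by interview, a subset that the intervention aims to enlarge. The comparison is biased against the intervention. A true move to earlier care is diluted, and where the effect is mainly to bring in late first attenders it can look like a delay. With other women's timing unchanged, the illustrative size is about 0 to +1.3 weeks. This rests on an assumed 5–25% of control women without a visit, 50–67% of them brought into care, and starts anywhere from 13 to 28 weeks. The documents supply none of these. No primary or secondary conclusion depends on the indicator.

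**What to change.** State that this indicator is analysed in all women with a 30 ± 2-week interview, and choose one of two estimands in advance:

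- **Proportion of all interviewed women whose first ANC visit is before one prespecified gestation**, with no visit counted as no, by the mixed logistic regression the protocol already provides for binary outcomes. The cut-off should be no later than the earliest interview, so that every woman's status is known.
- **Time to first ANC visit, censored at gestation at interview**, with clustering accounted for.

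These answer different questions. With an early cut-off, women brought in after it count as no in both arms, so late entry neither helps nor harms the comparison. The time-to-event form credits late entry as an improvement over none. Any mean in weeks among attenders should be reported as descriptive only, beside the proportion attending.

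The cost is a sentence or two in the analysis plan. The indicator already requires gestation at first visit, and gestational age at measurement is already a listed covariate, so no further data item should be needed. The loss is a simple mean difference in weeks.
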